### viii) Analysis

The results will stored on a SQL database and fed back to the researcher via the server that hosts the website. The data will be stored on the shared drive which will be password protected and only accessible to the researcher. Data will be retrieved, coded and inputted into computer software. Microsoft Office Excel 2007 will be used for data manipulation and SPSS version 16 for the main data analyses.

The usual descriptive statistics will be presented to summarise baseline characteristics of the study sample. Continuous variables such as age and level of cardiovascular risk will be summarised using mean and SD and/or median and quartiles. Binary variables such as gender and whether the respondent requests an electronic copy of their risk output for their GP will be summarised by counts and proportions. Summary statistics will be obtained for the study population as a whole, and for the four randomised groups, without formal testing of statistical significance of any differences between them.

The main analyses of efficacy will relate to the primary outcome measures: intention to change behaviour, understanding of risk information, emotional affect and worry about future heart disease. Summary statistics for the four groups will be presented, as above. The four groups will first be compared on an equal footing using one-way ANOVA. The three selected pairwise contrasts between the specified groups, will then be constructed (e.g. bar graph only v. pictogram; bar graph only v. metonym; and bar graph and preintervention questionnaire v. bar graph only).

Several secondary analyses will be performed. For the bar graph and preintervention questionnaire group (control group 1), paired analyses will be used to assess serial changes in outcome measures between pre- and postintervention questionnaires.

A multiple regression model will be used in a sub-group analysis to look for correlations between risk category on intention to change behaviour, understanding of risk and post worry about future heart disease outcomes, to see if responses are mediated by risk category. It will also be used to assess the correlational validity between intention to change behaviour, worry about future heart disease and understanding of risk information; to determine what level of worry increases intention to change behaviour and whether understanding also results in appropriate intentions. The subcomponents of the TPB (attitudes, perceived behavioural control and subjective norms) will also be examined, to see if they sufficiently predict intention to change behaviour (in order to test the efficacy of the model in predicting cardiovascular-related behaviour change).

The direct and indirect measures of intention to change behaviour will be correlated, to see whether those who report that they intend to change their behaviour actually take the opportunity to print out their risk output to take to their GP. Furthermore, a correlation between accurate understanding of risk information and confidence in understanding will be conducted. Lastly, Independent T-tests will compare baseline and post-intervention emotional affect and worry about future heart disease scores, to determine whether scores generally decrease after viewing a particular risk presentation format, or increase, demonstrating a possible negative impact.

For all analyses, point and interval estimates will be obtained, as well as p-values. In the event of substantial departure from Gaussian distributional form, transformation of scale and/or analogous non-parametric methods will be considered.

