One contender for representing gist information is the concept of a metonym. This is a type of metaphor and involves part and whole relations and associations. It is a word for a part of something, used to refer to the whole entity; or the whole is referred to in terms of something associated with it [42]. An example would be representing heart disease by using the concept of a myocardial infarction. Metonyms are important to everyday life as their concepts structure thoughts, attitudes and actions, as well as language [43]. Using a metonym to present future risk of a disease could be a way of improving affective forecasting, as people are not good at predicting the future [44]. It is a striking symbolisation what the disease encompasses, rather than an abstract numerical value. As far as we are aware, there are no existing studies that have used the metonym concept to present risk information.

The concept defined as correlational validity by Ubel [45], can be used to test whether individuals are applying their knowledge and understanding rationally. For example, men and women at high risk of heart disease should be more willing to take statins or blood pressure lowering drugs, than those at moderate or low risk. Therefore, it follows that if high risk individuals understand the risk information presented to them, they should be more likely to have greater intentions to change behaviour to reduce risk and vice versa.

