Before respondents can proceed, they will be given brief details about the study, asked to indicate their informed consent electronically and will be assessed for eligibility. The computer will then randomise the respondent into one of the four arms, ensuring allocation concealment (see Figure 1). These comprise a bar graph with pre-intervention questionnaire (control group 1), bar graph only (control group 2), pictogram (intervention group 1) or metonym (intervention group 2). Following the risk assessment, all respondents will be given their risk category (low, moderate or high) and the corresponding percentage figure (< 10%, 10-20% or > 20%). The main comparators will be the accompanying graphical risk presentation formats (bar graph, pictogram and metonym).

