**Figure 1 F1:**
[figure not shown]
**Flowchart of the RCT with intervention and control groups**.

The bar graph format to be used in the two control groups consists of vertical bar graph depicting percentages. This will be animated (growing upwards) to demonstrate the wide confidence intervals of the risk categories in the Personal Risk Score [47]. A bar graph has been chosen as it is the standard presentation format commonly used in current risk prediction tools. A pictogram of 100 hearts depicting natural frequencies will be used in intervention group 1. Research shows that these formats are better understood by patients, natural frequencies intuitively offer more insight than other formats [9,10] and pictograms help the viewer see the risk in context and facilitate accurate judgements of probability [48,49]. Again, this format will be animated, highlighting each affected heart in turn, to account for the range of numbers affected in the risk category. A metonym format will be used in intervention group 2. This will depict the seriousness of an emergency admission for a myocardial infarction. This has been chosen as heart disease is generally associated with having a myocardial infarction [50]. An image demonstrating healthy longevity will be shown to those in the low risk category; those at moderate risk will be shown an ambulance traveling towards a person's house, and a person being defibrillated will be shown to the high risk category.

To assess changes in emotional affect and worry, all respondents will have these measured at baseline during the risk assessment. Those in the bar graph and pre-intervention questionnaire group (control group 1) will also complete a partially parallel version of the post-intervention questionnaire. This is to address the Hawthorne effect of the four groups, and compare those who are asked to think about their cardiovascular risk and their prior intentions to reduce this, against those who are not. However, to keep the total number of items to a minimum, the focus is on reducing overall cardiovascular risk, instead of specific behaviours that lead to risk reduction. All respondents will view the risk in the format that they have been randomly assigned to and complete the post-intervention questionnaire.

There will be two main comparisons:

1. (a) Bar graph only v. Pictogram

(b) Bar graph only v. Metonym.

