*(ii) Understanding *- Items specific to the understanding of cardiovascular risk information have been developed and will be piloted, as no suitable validated scale currently exists. These comprise absolute probability perception e.g. *'What are your chances of having heart disease in the next 10 years?' *with three pre-defined response options (low, moderate, high*)*; subjective understanding of the risk information e.g. '*What should someone in your risk category do to reduce their risk of heart disease*?' with 3 pre-defined response options (do nothing to reduce their risk, try and do a little bit to reduce their risk, do as much as they can to reduce their risk); and confidence in understanding e.g. '*How confident are you that you have understood the risk information given to you?' *with a 7 point Likert Scale to indicate level of confidence in understanding.

*(iii) Emotional affect after viewing cardiovascular risk - *The Positive and Negative Affect Schedule- Short Form (PANAS-SF) will be used [56]. This is a 10-item truncated version of the PANAS, which has been well validated and cited in over 2,000 scholarly papers [57]. It was felt that the original 20-items would be too time-consuming and cognitively demanding for respondents, possibly leading to high drop out rates. As this study is interested in respondents' changes of affect after viewing their risk output, a slight adaptation to the wording of the instructions and anchors/pole labels was made to the post-intervention scale, to make it more logical. An example of one item is: '*Thinking about yourself right now at this present moment, to what extent do you feel upset?' *with a 5-point Likert response scale anchored *'not at all' *to *'extremely'*.

*(iv) Worry about future heart disease - *one item will be used to measure this construct, in order to keep the total time needed to complete the questionnaires to a minimum. No previously developed and validated scale regarding worry about future risk of heart disease currently exists. Therefore, the item was developed using previously validated scales relating to other health conditions, such the Lerman Breast Cancer Worry Scale [58] as a guide. This item is '*After viewing your results, how worried do you feel about developing heart disease in the future?*' with '*very worried' *to '*not at all worried' *anchored on a 7-point Likert response scale.

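### Affect and worry are compared between arms by one-way ANOVA without covariates, although baseline values exist for every respondent: valid, but less precise than it need be

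*Protocol article*

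**What the plan says.** The section viii) Analysis of the protocol article names the main efficacy analysis for intention, understanding, affect and worry: "The four groups will first be compared on an equal footing using one-way ANOVA". Three contrasts follow: bar graph only against pictogram, bar graph only against metonym, and the two bar graph groups against each other. No covariate is named.

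Section v) Intervention and comparisons, in the text after Figure 1, provides a baseline for two of these outcomes in all arms: "To assess changes in emotional affect and worry, all respondents will have these measured at baseline during the risk assessment". The same section makes risk category available for everyone: "Following the risk assessment, all respondents will be given their risk category (low, moderate or high"; section vi) lists it again among the respondent characteristics. Section vi) words both outcomes as measurements taken after the result is seen: "Emotional affect after viewing cardiovascular risk" and, for worry, "After viewing your results, how worried do you feel about developing heart disease in the future".

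These variables appear elsewhere in the Analysis section, but only in secondary work. Baseline affect and worry enter t-tests of baseline against post-intervention scores. Risk category enters a regression: "A multiple regression model will be used in a sub-group analysis to look for correlations between risk category on intention to change behaviour". Neither is described as an adjusted comparison of the arms. A pre-intervention measure of intention exists in control group 1 only.

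**The concern.** A baseline value of the outcome is usually the most useful covariate a trial has. Here it is collected from every respondent for the stated purpose of assessing change, and then left out of the comparison that decides between formats. Variation between respondents that was present before any format was shown stays in the error term, so intervals for the affect and worry contrasts are wider than the collected data require.

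Risk category is a second candidate. The Background expects it to matter for intention, on a condition: "if high risk individuals understand the risk information presented to them, they should be more likely to have greater intentions to change behaviour". That sentence does not mention worry, and the objectives treat the role of risk category as a question to be examined. It is therefore a reasonable covariate, but not one with a known effect.

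At stake is the trial's ability to separate the formats on two of its four primary outcomes, neither of which was used to set the sample size.

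**Working it through.** **1. The plan's own figure.** Section vii) gives SD 1.5, difference 0.5, α = 0.05 (two-sided assumed, as sidedness is not stated) and 200 per group for intention.

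- Standard error of a contrast: 1.5 × √(2/200) = 0.150.
- Power: Φ(0.5/0.150 − 1.960) = 91.5% (noncentral t: 91.4%), against the stated 90%.
- Required size for 90% power: 190 per group (191 by t), so 200 is sufficient. The figure reproduces.
- Detectable difference at 90% power with 200 per group: (1.960 + 1.282) × 0.150 = 0.486.

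**2. Baseline adjustment for affect and worry.** Let r be the correlation between baseline and post-viewing score. It is not in the documents; 0.3 to 0.7 is assumed. Adjustment multiplies the contrast variance by 1 − r², and the equivalent unadjusted group size is 200/(1 − r²). The SD of 1.5 is borrowed from intention, for illustration only, in the last two columns.

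| r | Variance factor | Equivalent n per arm | Standard error | Detectable difference, 90% power |
|---|---|---|---|---|
| none | 1.00 | 200 | 0.150 | 0.486 |
| 0.3 | 0.91 | 220 | 0.143 | 0.464 |
| 0.5 | 0.75 | 267 | 0.130 | 0.421 |
| 0.7 | 0.51 | 392 | 0.107 | 0.347 |

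A simulation of four groups of 200 (2,000 runs) gave variance ratios of 0.92, 0.73 and 0.49, in line with the formula.

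**3. What this means for power.** The gain depends on the true effect.

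- At the design effect of 0.5/1.5 = 0.33 SD, power is already 91.5% unadjusted and rises to about 94%, 97% and 99.7% at r = 0.3, 0.5 and 0.7.
- At 0.25 SD, an effect that is assumed here and appears nowhere in the protocol, it rises from 70% to 74%, 82% and 94%.

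**4. If change scores were meant.** The Analysis section does not say which score enters the ANOVA; the post-viewing score is inferred from the outcome definitions. With equal variances at both times, a change score has 2(1 − r) times the variance of the post score: 1.4, 1.0 and 0.6 at r = 0.3, 0.5 and 0.7. Baseline adjustment (0.91, 0.75, 0.51) is more precise at each value.

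**5. Intention.** Three arms have no pre-measure, so only risk category is available. With an assumed R² of 0.02, 0.05 or 0.10, the SD becomes 1.5 × √(1 − R²) and power goes from 91.5% to 92.0%, 92.8% or 94.0%, a gain of about 0.5 to 2.5 points.

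**The case against.** The strongest reply is that nothing here is an error. Randomisation makes the unadjusted ANOVA and its contrasts valid, and ordinary standard errors already allow for chance imbalance. A reader might infer bias, or an underpowered trial; the documents support neither, and the stated sample size reproduces. This stands, and limits the point to efficiency.

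Second, a journal article may leave covariates to a fuller document. Section vi) does promise one adjustment, for smoking items put only to current smokers. But this article does more than stay silent: it names a method that has no covariates and applies it to all four primary outcomes. Silence about stratified allocation, by contrast, is ordinary condensation, and nothing is built on it here.

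Third, a reader might infer that the plan cannot address change in affect at all. That goes too far. Baseline is collected for that purpose, and a secondary analysis asks whether scores fall or rise after a given format. What is absent is a comparison of the arms that uses baseline.

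Fourth, a reader might carry the largest gains over to every primary outcome. They do not apply to intention, on which the trial is powered, and the rise from 70% to 94% needs both the assumed 0.25 SD effect and the top of the assumed range of r.

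Fifth, adjustment has limits of its own. The understanding items with three response options do not suit a linear model. Smoking, activity and body mass index are already inputs to the risk score and overlap with risk category. The metonym image differs by risk category, so an additive term would not capture an effect that varies with it. Baseline is also taken after randomisation. All of this stands and is reflected in the fix.

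**Conclusion.** The point holds as a loss of precision, confined mainly to affect and worry. The arm comparison on these outcomes leaves out a baseline that is held for every respondent. If r is 0.3 to 0.7, the cost is 9% to 49% of the contrast variance, equivalent to 20 to 192 respondents per arm. Both ends rest on an assumed correlation. For intention the gain is small, about 0.5 to 2.5 power points under an assumed R² of 0.02 to 0.10.

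For the two format contrasts baseline adjustment is safe, since affect and worry are recorded before any format is shown and those arms have no pre-intervention questionnaire. For control group 1 against control group 2 it is safe only if baseline precedes that questionnaire. The text does not state the order; Figure 1, which was not available for this check, may show it.

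**What to change.** In section viii) Analysis:

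- **PANAS positive, PANAS negative and worry:** replace the one-way ANOVA by a linear model with arm, the baseline value of the same measure and risk category. Take the same three contrasts from it.
- **Intention:** add risk category only, and do not present this as more than a modest gain.
- **Understanding items with three response options:** make any adjusted model ordinal or logistic. This agrees with section vii), which says the analysis will respect the ordinal nature of the data.
- **Control group 1 against control group 2:** use baseline affect and worry as a covariate only if they are recorded before the pre-intervention questionnaire, and state that order. Otherwise leave this contrast unadjusted for baseline.

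The covariates are already collected, so the format contrasts need a change of analysis wording only, with no new data or recruitment. If baseline items currently follow the pre-intervention questionnaire in control group 1, moving them would be a small change to the website; leaving that contrast unadjusted for baseline avoids it.

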**Discussion:**

Having reviewed the literature, we are not aware of any other studies which have used the assessment of actual risk, in a trial to compare different graphical cardiovascular risk presentation formats. This trial will provide data about which graphical cardiovascular risk presentation format is most effective in encouraging behaviour change to reduce cardiovascular risk.

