## Aims and Objectives

The overall aim of this trial is to compare the effects of different graphical cardiovascular risk presentation formats on individuals' intention to reduce risk, understanding of risk information, emotional affect and worry about future heart disease, using a web-based risk calculator.

The primary objectives of this study are:

• To assess which format leads to the greatest intention to change behaviour.

• To determine which format best facilitates understanding of risk information.

• To analyse which format alters emotional affect.

• To assess which format induces worry about future heart disease the most.

• To examine the correlational validity between intention to change behaviour, understanding of risk and worry about future heart risk. To find out if understanding results in more appropriate intentions regarding cardiovascular risk and what level of worry increases intention to change behaviour.

• To determine whether intention to change behaviour, understanding of risk, and emotional affect are mediated by a person's risk category.

The secondary objectives of this study are:

• To examine the existence of the Hawthorne effect using two control groups.

• To analyse within group changes between pre and post-intervention responses in the group who completed both questionnaires.

• To evaluate the use of the internet-provided risk formatter (process evaluation), including analysis of web-logs.

• To assess the TPB's efficacy to predict intention to change behaviour to reduce future heart risk.

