This will enable a head-to-head comparison of the outcomes resulting from the different risk presentation formats.

2. Bar graph and pre-intervention questionnaire v. Bar graph only. Responses from viewing the bar graph and completing the baseline questionnaire will be compared with those from viewing the bar graph only. Additionally, within group changes between baseline and post-intervention questionnaires will be analysed in the group who completed both questionnaires (control group 1).

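### The primary objectives ask which of three formats is best, but no contrast between pictogram and metonym is planned

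*Protocol article*

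**What the plan says.** Under Aims and Objectives, the protocol article lists among its primary objectives "To assess which format leads to the greatest intention to change behaviour", "To determine which format best facilitates understanding of risk information" and "To assess which format induces worry about future heart disease the most". The Discussion part of the abstract carries the same promise into the conclusion: "This trial will provide data about which graphical cardiovascular risk presentation format is most effective in encouraging behaviour change".

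Methods/Design, v) Intervention and comparisons, names two format comparisons, "1. (a) Bar graph only v. Pictogram" and "b) Bar graph only v. Metonym", and comments: "This will enable a head-to-head comparison of the outcomes resulting from the different risk presentation formats". The other main comparison there sets the two bar-graph arms, with and without the pre-intervention questionnaire, against each other.

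Section viii) Analysis plans summary statistics for all four groups and a one-way ANOVA over the four groups, and then: "The three selected pairwise contrasts between the specified groups, will then be constructed". The three contrasts listed are the two above and the questionnaire contrast. The list opens with an e.g., but the text gives the number as three, names three, and they match section v). The list is therefore closed, and pictogram against metonym is not on it.

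**The concern.** An objective that asks which of three formats comes out on top concerns all three pairs of formats. The plan covers two of them. The ANOVA does not supply the third. It has four arms, two of which show the same bar graph, and a significant result does not say which arms differ. The difference could even lie between the two bar-graph arms.

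Two outcomes would leave the question open. If both new formats beat the bar graph, nothing planned says which is better. If only one contrast is significant, it is tempting to name that format the winner. A significant result beside a non-significant one is not evidence that the two formats differ. At stake is the conclusion that the article offers to developers of risk prediction tools.

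**Working it through.** **Inputs.** From section vii) Sample size calculation: SD about 1.5, 200 per group, difference 0.5 point, alpha 0.05, power 90%. Assumed: two-sided tests (the article does not say), and every true gain other than the 0.5 points of section vii).

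**1. The plan's own figure.** The standard error of a difference between two arms is 1.5 × √(2/200) = 0.15. Power for 0.5 points is Φ(0.5/0.15 − 1.96) = Φ(1.37) = 0.915. For exactly 90% power, 190 per group are needed. The stated 200 is therefore sufficient, as the article says.

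**2. The missing contrast.** Pictogram and metonym also have 200 each, so the standard error is again 0.15, power for 0.5 points is again about 91%, and the 95% confidence interval has half-width 1.96 × 0.15 = 0.29.

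**3. Two equally effective new formats.** Let both exceed the bar graph by d. Each planned contrast is significant with probability p = Φ(d/0.15 − 1.96). The two contrasts share the bar-graph-only arm, so their correlation is 0.5, and the probability that both are significant follows from the bivariate normal distribution. Exactly one is significant with probability 2 × (p − both).

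| d (assumed for both formats) | p | both significant | exactly one significant | exactly one, if a significant four-arm ANOVA is required first |
|---|---|---|---|---|
| 0.50 | 0.915 | 0.856 | 2 × (0.915 − 0.856) = 0.12 | 0.11 |
| 0.35 | 0.646 | 0.491 | 2 × (0.646 − 0.491) = 0.31 | 0.25 |
| 0.30 | 0.516 | 0.349 | 2 × (0.516 − 0.349) = 0.33 | 0.24 |

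The last column is from 400,000 simulated trials per row, with the questionnaire arm equal to bar graph only. The article says only that the ANOVA comes first, so treating it as a gate is an assumption.

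**4. Unequal new formats.** With assumed gains of 0.25 (pictogram) and 0.5 (metonym), metonym alone is significant in about 54% of simulated trials. In about 44% of those, the direct difference between pictogram and metonym is not significant.

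**5. An optional gate.** Suppose an omnibus test over bar graph only, pictogram and metonym precedes the three format pairs, each tested at 0.05. The simulated family-wise error for those three pairs on one outcome is 5.0%. Adding the questionnaire contrast at 0.05 outside the gate brings it to about 9%. Power for a 0.5-point contrast is about 90% when one format lies 0.5 above two equal ones. With means of 0, 0.25 and 0.5, power for bar graph only against metonym is about 85%, compared with 91% without the gate.

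**The case against.** The bar graph is described as the standard format and its arms as controls. Comparing each new format with a standard is a conventional design, and the contrasts follow it. On that view the fault lies in the wording of the objectives, not in the analysis. This stands to the extent that rewording the objectives is an equally good cure. It does not remove the mismatch, because objectives and conclusion as written ask for a best format.

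A reader might infer that the trial cannot answer its primary objective at all. The article does not support that. Both new-format arms are randomised concurrently with 200 respondents each, summaries of all four groups will be reported, and the pictogram-minus-metonym estimate is the difference of the two planned contrasts. If the bar graph proves best, the planned contrasts settle the matter. The article does promise point and interval estimates for all analyses, but this contrast is not among the analyses it lists, and a comparison chosen after the means are seen is weaker evidence than a pre-specified one.

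A reader might also take 31% or 33% as the rate of falsely declared winners. Those figures depend on assumed gains. At the article's own 0.5 points the figure is 12%, and the article nowhere says that a winner will be declared from one significant and one non-significant contrast.

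**Conclusion.** The point holds in a limited form. Three primary objectives and the stated conclusion call for a ranking of three formats, but the closed list of contrasts never sets pictogram against metonym. The analysis as written cannot formally establish which of the two is better when both, or only one, differ from the bar graph.

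If the two new formats are in truth equal, the planned contrasts split (one significant, one not) in about 12% to 33% of trials over gains of 0.5 down to 0.30, or about 11% to 25% if the ANOVA acts as a gate. At a gain of 0.5 for both, about 86% of trials show both significant and leave the two unranked. These figures rest on SD 1.5, 200 completers per arm, two-sided 0.05 and the assumed gains.

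Randomisation, sample size and data collection are unaffected. The defect lies in the analysis specification and can be cured before analysis.

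**What to change.** Do one of the following before the data are analysed:

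- Pre-specify pictogram against metonym as a further contrast, with point estimate, 95% confidence interval and p-value. It needs no extra respondents. The cost is one more comparison to report and interpret.
- Reword the objectives and the conclusion as each new format against the bar graph, and drop the claim to identify the most effective format.

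If the contrast is added, state how multiplicity is handled. The three-arm omnibus gate is optional. It holds family-wise error at 5% only for the three format pairs on a single outcome, and it covers neither the questionnaire contrast nor the four primary outcomes. It gives power of about 90% to 85% for a 0.5-point contrast, depending on the pattern of means. If alpha were instead divided equally over four contrasts (0.0125 each), power for 0.5 points would be about 80%. Divided over the three already planned, it would be about 83%.

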### vii) Sample size calculation

For simplicity, the sample size calculation is based on a comparison of means, though the analysis will recognise the ordinal nature of the data. It is hard to speculate on the difference between the groups and so the sample size is based on comparing 2 groups on the primary outcome measure which is intention to change behaviour; this will give a group size which will be used for all the groups. Recruitment will continue until 800 respondents (200 in each group) have completed the trial. The likely uptake rate is unknown and a number of the suggested recruitment methods may be needed. Based on a study that used a similar Likert Scale scoring system for a different risk context [59], the scores on intention to change behaviour within a group should have an SD of about 1.5. The total sample size in each group of 200 would then be sufficient to detect a difference of 0.5 point between two groups, with 90% power and significance value of *α = *0.05.

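### Baseline and post-intervention affect and worry come from the same respondents but are to be compared with independent t-tests, so the standard errors, p-values and intervals for change are wrong (secondary analysis; should be fixed)

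*Protocol article*

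**What the plan says.** Section v (Intervention and comparisons), in the text after Figure 1, sets up the repeated measurement: "To assess changes in emotional affect and worry, all respondents will have these measured at baseline during the risk assessment". It then adds: "All respondents will view the risk in the format that they have been randomly assigned to and complete the post-intervention questionnaire". Every completer, in all four arms, therefore has a baseline and a post-intervention score for affect and for worry.

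Section viii (Analysis) names the test for comparing them: "Independent T-tests will compare baseline and post-intervention emotional affect and worry about future heart disease scores". The stated purpose is "to determine whether scores generally decrease after viewing a particular risk presentation format, or increase, demonstrating a possible negative impact".

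Earlier in the same section, for control group 1, the method for pre/post change is different: "paired analyses will be used to assess serial changes in outcome measures between pre- and postintervention questionnaires".

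The section closes its list of analyses with a general commitment: "For all analyses, point and interval estimates will be obtained, as well as p-values".

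The comparison of formats on affect and worry is handled elsewhere in section viii, by a four-group one-way ANOVA followed by three selected pairwise contrasts. Those are the main efficacy analyses.

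**The concern.** An independent-samples t-test assumes that the two sets of scores come from unrelated people. Here each respondent contributes one score to each set. Ignoring the within-person correlation gives the wrong variance for the mean change, and so a wrong p-value and a wrong interval.

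The protocol is also inconsistent. It treats pre/post data as paired in control group 1 and as independent two paragraphs later. If the outcome measures analysed in control group 1 include affect and worry, that arm has two incompatible methods for the same data.

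The consequence is practical because this comparison is the protocol's stated check on whether seeing one's risk in a given format has an adverse emotional effect. With a positive correlation the error makes small rises in worry or negative affect harder to detect. Since intervals are promised for every analysis, intervals that are too wide would also be published.

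**Working it through.** **The plan's own figure.** Section vii (Sample size calculation) says "the scores on intention to change behaviour within a group should have an SD of about 1.5". It concludes: "The total sample size in each group of 200 would then be sufficient to detect a difference of 0.5 point between two groups". The power claimed is 90%, at α = 0.05. Two-sided testing is assumed, since sidedness is not stated.
- Standard error of the difference = 1.5 × √(2/200) = 0.150.
- Power = Φ(0.5/0.150 − 1.96) = Φ(1.373) = 0.915.
- The required size by the same formula is 190 per group, so 200 is sufficient.

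The sample size reproduces and is not affected by this point.

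**Inputs for the check.**
- n = 200 in one arm (section vii).
- Baseline and post-intervention SDs equal; where points are used, 1.5. This is an assumption, borrowed from the intention score.
- Pre/post correlation r = 0.3, 0.5 or 0.7. This is an assumption; the protocol gives none.

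**Formulas.**
- Standard error used by the independent test: SD × √(2/n) = 0.150, whatever r is.
- Correct (paired) standard error: SD × √(2(1 − r)/n).
- Ratio of interval widths: 1/√(1 − r).
- True type I error of the nominal 5% independent test: 2 × [1 − Φ(1.96/√(1 − r))].
- Power of the independent test at a true change of d SDs: Φ((d/√(2/n) − 1.96)/√(1 − r)).
- Power of the paired test: Φ(d/√(2(1 − r)/n) − 1.96).

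**Results, with d = 0.2 for the power columns** (0.3 point at SD 1.5; an illustrative value that is not in the protocol).

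| r | Correct SE | 95% half-width, independent / paired | Width ratio | True type I error | Power, independent | Power, paired |
|---|---|---|---|---|---|---|
| 0.3 | 0.126 | 0.294 / 0.246 | 1.20 | 1.9% | 52% | 67% |
| 0.5 | 0.106 | 0.294 / 0.208 | 1.41 | 0.6% | 52% | 81% |
| 0.7 | 0.082 | 0.294 / 0.161 | 1.83 | 0.03% | 53% | 95% |

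Worked line for r = 0.5:
- Width ratio: 1/√0.5 = 1.41.
- Type I error: 2 × [1 − Φ(1.96/0.707)] = 0.006.
- Independent power: Φ((2 − 1.96)/0.707) = Φ(0.057) = 0.52.
- Paired power: Φ(2/0.707 − 1.96) = Φ(0.868) = 0.81.

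A simulation of 10,000 trials per setting agreed. Type I error of the independent test was 1.8%, 0.6% and 0.03%, and that of the paired test was about 5% throughout.

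**Sensitivity.**
- At r = 0 the two tests coincide.
- At r = −0.2 the independent test would be anti-conservative, with type I error 7.4%. A negative correlation between one person's two scores in one online study is implausible.
- For a larger change of 0.5 point, or 0.333 SD (the size section vii uses for intention, borrowed here), the independent test has 95.0%, 97.4% or 99.4% power at r = 0.3, 0.5 or 0.7. The paired test has 97.9%, 99.7% or more than 99.9%. The loss of power matters for small changes only.

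**The case against.** The best defence is that little depends on this test. It is the last of several secondary analyses. With complete pairs the mean change is estimated without bias. Under any plausible correlation the error is conservative, so it creates no false positives. Affect and worry are compared between formats by the ANOVA and the randomised contrasts, which are sound. The size of the error also depends on a correlation the document does not give. All of this stands and limits the severity. None of it makes the named test right.

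One might read the sentence as independent t-tests of change scores between formats. The text does not say so: it compares baseline with post-intervention scores, to see whether they fall or rise after a format. If change scores were meant, the sentence still needs rewriting. The allowance for transformation or non-parametric methods is no remedy either, because it is triggered by non-Gaussian data and does not address dependence.

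Two stronger readings are tempting and are not supported.
- A reader might infer that the plan will miss real rises in worry or negative affect. That depends on the size of the rise: a 0.2 SD change is detected about half the time, and a 0.333 SD change nearly always.
- A reader might infer that formats will be ranked by which arm's own change reaches significance. The protocol does not say this. It asks a within-format question here and assigns the comparison of formats to the between-arm contrasts.

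**Conclusion.** The point holds as a definite but contained error: section viii names a test for unrelated samples where section v makes the data paired, and section viii itself uses paired methods for control group 1. Nothing else in the document corrects it.

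The affected quantities are the standard errors, p-values and intervals for within-arm change in affect and worry. The width ratios and type I errors in the table depend only on the assumed correlation and equal SDs; the power figures also depend on 200 per arm and on the chosen effect size. The direction is firmer than the amount: any positive correlation makes the stated intervals too wide and the check for an adverse emotional effect less sensitive to small rises. No primary comparison and no sample size figure changes. It should be fixed, but it does not threaten the trial's main conclusions.

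**What to change.** In section viii, replace the independent t-tests with paired t-tests, or the Wilcoxon signed-rank test if the differences are clearly non-Gaussian, for within-arm change in affect and worry. Report the mean change with its interval. Bring this into line with the paired analyses specified for control group 1, and say whether those cover affect and worry, so that one method applies to that arm.

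Add that any statement that one format raises or lowers affect or worry more than another will rest on the between-arm contrasts already planned. Adjusting those contrasts for the baseline score collected on everyone is an optional gain in precision; the unadjusted contrasts are valid under randomisation.

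The cost is a sentence or two of text. No new data, recruitment or questionnaire change is needed.
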